**Fig. 1 Fig1:**
[figure not shown]
EPIC El Rio Families Participant Anticipated Enrollment and Study Design

This design is responsive to standards of care for T2DM prevention [44] and will provide the opportunity to investigate pre−/post-intervention effects, intervention versus control effects, and maintenance effects. The number of participants and design also allow us to evaluate processes critical to successful implementation by El Rio, informing future replication and the potential scaling of the intervention to other sites in this and other FQHC networks. This clinical trial (ClinicalTrials.gov identifier NCT03781102) has been approved by the University of Arizona Institutional Review Board and all participants will provide informed consent or assent prior to participation.

Changes in percent weight for the mothers and changes in the BMI z-score for the children are used to confirm that there is adequate statistical power with the sample size of *n* = 60 dyads. For mothers, the calculation is based on the observed change in the DEPLOY study for both sexes [34]. The mean change in body weight after 6 months was − 6.0% (standard deviation = 4.0%). For children, the calculation is based on data from the EPIC Kids Study in which the mean change in BMI z-score was 0.054 (standard deviation = 0.02) [32]. The power calculation assumed that in each period (intervention versus wait-list control) there will be 3 groups with 10 dyads per group (*n* = 30 intervention versus *n* = 30 wait-list control). The statistical power is > 80% for the mothers and 95% for the children assuming an intra-group correlation or 0.15 or below (two-sided alpha level of 0.05). As this is a pilot study to provide estimates for a larger trial, there is no adjustment for multiple comparisons.

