The home food and physical activity environment will be assessed using the *Family Nutrition and Physical Activity Tool,* a 21-item survey of the family home environment and practices associated with children’s risk of becoming overweight. Parents will use the tool to report the frequency of breakfast and family meals, modeling of nutrition, nutrient dense foods and high calorie beverages, restriction and reward, parent modeling physical activity, child’s physical activity, screen time, TV in bedroom, and sleep routines [59, 60].

Given the considerable impact of social and environmental factors on participants’ ability to follow through with health recommendations, we will collect demographic and socioenvironmental data associated with T2DM risk and health disparities (e.g., food insecurity, housing stability, culture and language, community support, socioeconomic status, financial barriers, literacy and numeracy) using the PRAPARE questionnaire developed for use in health care settings, and already routinely implemented by El Rio. All surveys will be made available in English and Spanish.

The intention-to-treat principle will be used for all the analyses. Differences in participants’ baseline characteristics between the two groups will be evaluated by a two-sample *t*-test for continuous outcomes and by Chi-square test or Fisher’s exact test for categorical outcomes. Initial analyses will compare the changes between baseline and follow-up between the intervention versus wait-list control groups using two-sample sample *t*-tests. Subsequently, a mixed-model analysis of covariance including treatment group, time, and baseline value of the outcome will be used to assess the effects of intervention at 13 and 26 weeks. Participants will be treated as a random effect nested within group. An interaction effect between time and treatment group will be assessed first. If there is no interaction effect, the overall treatment difference will be assessed. Otherwise, the treatment difference will be assessed at each time point. In order to measure the relative cost-effectiveness of these programs, we will also explore costs associated with implementation by El Rio staff.

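### The t-tests, and the mixed model as worded, do not account for the session-group clustering that the sample size allows for; at the assumed upper-bound ICC of 0.15 a nominal 5% t-test has about 13% to 21% type I error

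*Protocol article*

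**What the plan says.** All of this is in the protocol article, Methods/design, under the evaluation of the study.

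- **Design and delivery.** The trial is described as group randomized. One of two clinics is allocated to each condition by coin flip, and the programme is delivered in group sessions of up to 15 dyads. Wait-list dyads start the programme after week 13.
- **Sample size.** In each condition "there will be 3 groups with 10 dyads per group", and power is given "assuming an intra-group correlation or 0.15 or below", with a "two-sided alpha level of 0.05". The result is stated as "The statistical power is > 80% for the mothers and 95% for the children".
- **First analysis.** "Initial analyses will compare the changes between baseline and follow-up between the intervention versus wait-list control groups", by two-sample t-tests. No adjustment for session group is mentioned.
- **Second analysis.** A mixed-model analysis of covariance with treatment group, time and baseline value, assessing effects at 13 and 26 weeks. Its random part is described in one sentence: "Participants will be treated as a random effect nested within group". No session-group variance is named.

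**The concern.** The sample size section accepts that members of one session group may have correlated outcomes. A two-sample t-test on individuals treats all 60 mothers (or children) as independent. A participant random effect ties together one person's measurements at 13 and 26 weeks, but gives no shared variance to different people in the same session group. If that is the only random effect, neither analysis reflects the correlation that the trial was sized for.

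Standard errors would then be too small and intervals too narrow. That matters in a pilot too, because the article says the trial is meant to provide estimates for a larger one, and the precision of those estimates is part of what the next trial will use.

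**Working it through.** **Inputs, all from the sample size paragraph:** 3 groups of 10 per condition (30 per condition), ICC up to 0.15, two-sided alpha 0.05; mothers' mean change 6.0% with SD 4.0% (standardised 1.5); children's 0.054 with SD 0.02 (standardised 2.7).

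**1. The plan's own power figure.**
- Design effect: 1 + (10 − 1) × 0.15 = 2.35. Effective size: 30 / 2.35 = 12.77 per condition.
- Standard error of the difference in SD units: √(2 / 12.77) = 0.396. Noncentrality for mothers: 1.5 / 0.396 = 3.79.
- Power for mothers: 80.6% by noncentral t on 2 × 3 − 2 = 4 df; 96.1% on 58 df; 96.6% by the normal approximation.
- Power for children: 99.8% on 4 df, essentially 100% on 58 df.

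The 4-df result sits just above the stated 80% for mothers. The children's 95% is not reproduced by either choice.

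**2. Type I error of the individual-level t-test.** If clustering inflates the variance of the difference by a factor V, the error is approximately 2 × [1 − Φ(1.96 / √V)].
- Both conditions clustered: V = 2.35, so 1.96 / 1.533 = 1.279, giving 20.1%.
- Intervention condition only: V = (2.35 + 1) / 2 = 1.675, so 1.96 / 1.294 = 1.514, giving 13.0%.

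Simulation of the t-test itself, 200,000 replicates per scenario, 3 groups of 10:

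| ICC | Intervention only clustered | Both clustered |
|---|---|---|
| 0.15 | 13.4% | 20.9% |
| 0.10 | 10.5% | 15.9% |
| 0.05 | 7.7% | 10.5% |
| 0.01 | 5.5% | 6.0% |

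With 2 groups of 15, which the session limit permits, ICC 0.15 gives 17.6% and 27.9%.

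**3. Understatement of the standard error at ICC 0.15.** Both clustered: 1 − 1/√2.35 = 35%. Intervention only: 1 − 1/√1.675 = 23%.

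**4. The mixed model, if participant is its only random effect.** In a balanced layout, and setting baseline adjustment aside, the overall treatment test is close to a t-test on each person's mean over the two visits. The article gives no within-person correlation, so 0.5 to 0.9 is assumed here. At ICC 0.15, with the group effect persisting over both visits, the error is 13.5% to 15.8% (one condition clustered) or 21.7% to 25.2% (both). On that reading the second analysis does not repair the first.

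**5. A test that respects the grouping.** A t-test on six group means with 4 df has simulated error of 5.0% at ICC 0.15 and, from step 1, 80.6% power for mothers. This assumes three real groups per condition and no separate site variance.

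**The case against.** Several points on the other side stand.

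- **The mixed-model sentence is ambiguous.** The same paragraph writes treatment group in full when it lists model terms, and the sample size paragraph uses group for session groups. The sentence could therefore mean participants within session groups, with the group variance left to a fuller document. The same paragraph also calls the two conditions groups, so neither reading is certain. A reader might infer that the mixed model definitely ignores clustering; the text does not establish that. The ambiguity does not help the t-tests.
- **The ICC is a ceiling.** The article allows 0.15 or below. At 0.01 the inflation is almost negligible. It gives no basis for expecting so low a value, but the 13% to 21% range belongs to the ceiling.
- **Controls do not meet before week 13.** On that fact the lower end of each range is the more natural one at week 13. The upper end follows the article's own assumption of three groups in each condition.
- **The power match is not proof.** A reader might infer from 80.6% that a 4-df cluster-level test was assumed. The statement is an inequality that 96% also satisfies, and the children's figure fits neither calculation.
- **It is a pilot.** Strict type I error control is not the main criterion, and the article makes no multiplicity adjustment. The width of the intervals still matters for planning the next trial.

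A reader might also conclude that false-positive findings on weight, HbA1c and behaviours are likely. An error rate of 13% to 21% does not make a false positive likely for any one outcome, and the article gives no ICC specific to HbA1c or behaviours.

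**Conclusion.** The point holds as a mismatch within the article. The sample size allows for correlation within session groups; the t-tests certainly ignore it, and the mixed model as worded does so unless a session-group variance is also intended. The t-test figures rest on 3 groups of 10, equal group sizes and normally distributed outcomes. At ICC 0.15 the error is about 13% (intervention only clustered) to 21% (both); at 0.05 about 8% to 10%; at 0.01 about 5.5% to 6%. The mixed-model figures also depend on the participant-only reading and an assumed within-person correlation.

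This is not merely detail that an article may leave to an analysis plan, because the article itself states the tests and the random effect. There is, however, a limit on what correcting it achieves. With one site per condition, site variance cannot be separated from treatment. For illustration, suppose 0.02 or 0.05 of the variance, out of a total intra-group share of 0.15, lay between sites (assumed values). The between-group variance of a condition mean would be (0.13 + 0.085)/3 = 0.0717 or (0.10 + 0.085)/3 = 0.0617. The true variance would then exceed the estimated one by a factor of 1 + 0.02/0.0717 = 1.28 or 1 + 0.05/0.0617 = 1.81, and even the 4-df test would have about 7.0% or 10.8% error.

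**What to change.** 1. Make the unadjusted two-sample t-tests descriptive, without inferential p-values.
2. Name the mixed model as the primary analysis. State an explicit session-group random effect in addition to participant, with Kenward-Roger or Satterthwaite degrees of freedom, and say what group means in the nesting sentence.
3. **Week 13:** model clustering in the intervention condition, with wait-list dyads as singletons. Alternatively, and only if controls are assigned to their session groups in advance, compare group means on 4 df. These two options should not be mixed.
4. **Week 26:** include session group in both conditions, because controls will by then have had the group programme.
5. State that site variance is confounded with treatment, so the corrected intervals exclude it.

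**Cost:** analysis wording and a few lines of code; no change to recruitment or data collection. The real price is precision. For mothers at ICC 0.15, with 30 per condition and SD 4.0%, the naive 95% half-width is 2.00 × √(2/30) × 4.0 = 2.1 percentage points. The group-means version on 4 df gives 2.78 × 0.396 × 4.0 = 4.4 percentage points.

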## Discussion

There is a growing need to develop and evaluate prevention initiatives that focus on lifestyle modification for youth and their families at highest risk for T2DM. We will, in collaboration with an FQHC, create a T2DM risk-reducing intervention program (*EPIC El Rio Families*) for delivery to mothers at high risk for T2DM because of their history of GDM and/or prediabetes, and who have school-aged children who are also at risk. The intervention is unique in that it was designed at its inception to integrate with the clinical operation of an FQHC and developed in partnership with client-facing health and wellness FQHC staff. FQHCs by their nature are well suited to implement interventions for populations who have historically experienced significant barriers to accessing quality health care. Past diabetes prevention studies implemented in medical centers were efficacy trials that gave minimal consideration to the cost of implementation [22–24]. These research-oriented programs were then adapted to be used in community settings [35]. As a result, they are often not optimized for dissemination in large volume primary care settings. Moreover, very few have simultaneously targeted mothers and their children at risk for T2DM. By designing the program to be implemented in an extant FQHC facility that cares for families, we will be able to answer several questions that are crucial to developing an effective translation model that can be applied across the FQHC system. The results from this study will be critical in developing a T2DM prevention model that can be implemented and scaled across FQHC settings to effectively mitigate this burgeoning problem in medically underserved youth and adult. In this context, using the FQHC system to implement diabetes prevention programs in populations that have an increased burden from T2DM is an important public health initiative.

## Data Availability

Not applicable.

## Abbreviations

EPIC: Encourage, Practice and Inspire Change
DPP: Diabetes Prevention Program
GDM: Gestational diabetes mellitus
T2DM: Type 2 diabetes mellitus
FQHC: Federally Qualified Health Center
CDC: Centers for Disease Control and Prevention
YMCA: Young Men’s Christian Association
CLIA: Clinical Laboratory Improvement Amendments
HbA1c: Hemoglobin A1c
BMI: Body Mass Index
